# Aspin: neurosurgical aspirin intervention prognostic study — perioperative continuation versus discontinuation of aspirin in lumbar spinal surgery, a randomized controlled, noninferiority trial

**DOI:** 10.1186/s13063-024-07945-w

**Published:** 2024-02-29

## Abstract

**Rationale:**

Aspirin is typically discontinued in cranial and spinal surgery because of the increased risk of hemorrhagic complications, but comes together with the risk of resulting in an increase of cardiac and neurologic thrombotic perioperative events.

**Objective:**

The aim of this study is to investigate the non-inferiority of perioperative continuation of aspirin patients undergoing low complex lumbar spinal surgery, compared with the current policy of perioperative discontinuation of aspirin.

**Study design:**

A randomized controlled trial with two parallel groups of 277 cases (554 in total).

**Study population:**

Patients undergoing low complex lumbar spinal surgery and using aspirin. All patients are aged >18 years*.*

**Intervention:**

Peri-operative continuation of aspirin.

**Study outcomes:**

Primary study outcome: composite of the following bleeding complications:Neurological deterioration as a result of hemorrhage in the surgical area with cauda and/or nerve root compression.Post-surgical anemia with hemoglobin level lower than 5 mmol/l, requiring transfusion.Subcutaneous hematoma leading to wound leakage and pain higher than NRS=7.Major and/or minor hemorrhage in any other body system according to the definition of the International Society on Thrombosis and Haemostasis bleeding scale.

Secondary study outcomes:Each of the individual components of the primary outcomeAbsolute mean difference in operative blood loss between the study armsThrombo-embolic-related complications:Myocardial infarctionVenous thromboembolismStrokeArterial thromboembolism

**Further study outcomes:**

Anticoagulant treatment satisfaction by the Anti-Clot Treatment Scale (ACTS) and general health by the Patient-Reported Outcomes Measurement Information System (PROMIS Global-10) in the pre- and postoperative phase.

**Nature and extent of the burden and risks associated with participation, benefit, and group relatedness:**

Participation in this study imposes no additional risk to patients. Currently, there is no consensus on whether or not aspirin should be discontinued before cranial or spinal surgery. Currently, aspirin is typically discontinued in cranial and spinal surgery, because of a potential increased risk of hemorrhagic complication. An argument not based on a clinical trial. However, this policy might delay surgical procedures or carry the risk of resulting in an increase in cardiac and neurologic thrombotic perioperative events. It is unclear if the possibility of an increase in hemorrhage-related complications outweighs the risk of an increase in cardiac and neurologic thrombotic perioperative events.

Furthermore, the Data Safety Monitoring Board (DSMB) will be asked for safety analysis by monitoring the study.

There are no further disadvantages to participating in this study. Outcome measurements are recorded during admission and regular outpatient visits, and thus, do not require additional visits to the hospital.

## Introduction and rationale

Current guidelines regarding the safety of the perioperative (dis)continuation of aspirin for surgical procedures fail to provide clear recommendations regarding patients undergoing cranial and spinal surgery. Currently, aspirin is discontinued in cranial and spinal surgery because of a potential increased risk of hemorrhagic complications. However, this policy might delay surgical procedures and carries the risk of resulting in an increase in cardiac and neurologic thrombotic perioperative events. It is unclear if the possibility of an increase in hemorrhage-related complications outweighs the risk of an increase in cardiac and neurologic thrombotic perioperative events. Therefore, a randomized controlled trial is required.

Cardiovascular diseases (CVDs) are the primary cause of death in developed countries and are expected to be the leading cause of death worldwide [1]. Cardiovascular diseases are a group of illnesses including myocardial infarction, coronary heart disease, and stroke. In the primary and secondary prevention of CVDs anticoagulant drugs play a key role, with aspirin being the most commonly used [1–3]. Specifically for the Netherlands, aspirin is prescribed for circa 230,000 patients annually [4]. With the increasing incidence of CVDs, the usage of anticoagulant drugs will increase forming a problem during surgical intervention.

Currently, there is no consensus on whether aspirin should be discontinued before neurosurgical intervention. One of the arguments leading the discussion is the POISE-2 trial by Devereaux et al., in which the conclusion was that procedural continuation of aspirin did not reduce the rates of all-cause mortality of non-fatal myocardial infarction. But it does come together with increased risks of major bleedings [5].

These results are supported by two reviews that included mostly non-RCT studies.

A review and meta-analysis by Burger et al. in non-cardiac surgery showed a significant increase of procedural bleeding complications, without a significant reduction nor increase of death or nonfatal myocardial infarctions. A low dose of aspirin did not significantly differ in bleeding risk or complications or mortality related to it [6]. The same was concluded in the review of Kiberd and Hall [7].

Another interesting pharmacological phenomenon is the aspirin withdrawal rebound effect, the hyperactivity of platelets after the interruption of aspirin [8]. Even though there is limited knowledge supporting this effect, it leads to clinical caution to discontinue aspirin. Multiple cases in different surgical fields describe fatal thrombo-embolic complications after discontinuing aspirin perioperatively. Limited knowledge is available about the pharmacokinetic availability of aspirin after interruption and the regaining of platelet function thereafter. A small study by Alcock et al. showed, in healthy participants, no evidence for a rebound phenomenon which leaves this argument open for discussion [9].

These results are contrasted by the study of Oscarsson et al. [10]. This randomized, double-blinded, placebo-controlled trial studied the effects of discontinuing aspirin on the occurrence of major adverse cardiac events together with hemorrhagic complications in a diversity of surgical interventions. This study showed a significant reduction in cardiac events perioperatively, a risk reduction of 7.2%, and no difference in hemorrhagic complications were found. Note bene, this difference is statistically not significant because of an early termination of inclusion. Additionally, this difference is based on mainly patients undergoing abdominal, urologic, orthopedic, and gynecologic surgery that are known as immobile patients post-operatively leading to a higher thrombo-embolic risk and are not completely comparable to neurosurgical patients undergoing spinal surgery which is often improving mobility by pain reduction and motor control. In addition to these results, the CLASP study, a gynecological randomized trial studying the effects of low-dose aspirin in the prevention and treatment of pre-eclampsia in pregnant women, did not observe an increase in uterine, placental or fetal hemorrhagic complications in the study group [11]. Unfortunately, these studies did not include any neurosurgical cases. This restricts the little evidence for continuing aspirin in neurosurgical cases and leads to more interest and concern in this matter.

A systematic review and meta-analysis regarding the safety of aspirin continuation in spinal surgery was conducted by our research group [12]. Only three non-randomized studies, including 370 patients undergoing cervical, thoracic, and lumbar spine surgery were identified. No significant differences in mean perioperative blood loss were seen between the aspirin-continuing group and the aspirin-discontinuing group. Similar non-significant differences between the two groups were found for cardiac events, stroke, and surgical site infections [13–15].

In addition to spinal surgery, the evidence in cranial surgery is even more limited. A comparative study by Rahman et al. in 83 patients undergoing craniotomy for brain tumor demonstrated no increased risk of perioperative hemorrhage-related complications among patients continuing aspirin [16]. Additionally, an observational study by Palmer at all, found no association between aspirin and postoperative hemorrhage [17]. In case of cerebral aneurysmatic pathology, aspirin is recommended for unruptured aneurysms and prevents ruptures by its anti-inflammatory effects [18]. In a ruptured aneurysm with subarachnoidal hematomas continuation versus discontinuation of aspirin did not lead to significant differences in bleeding risk, bleeding-related complications, or prevention of secondary ischemia due to vasospasms [19, 20].

In conclusion, there is a paucity of studies regarding the safety of the continuation of aspirin during cranial and spinal procedures, and the available evidence is of low methodologic quality. The hypothesis is that potential bleeding complications in cranial and spinal surgery might exceed the risks reported in other surgical literature. Especially in cranial surgery, postoperative bleeding may be catastrophic due to the confined space and vulnerability of the surrounding structures, but no studies exist to support this hypothesis. The current clinical practice in patients on aspirin and due to undergo a cranial or spinal is to discontinue aspirin 5 days prior to surgery. There is no clinical evidence to support this policy. Therefore, we propose a randomized controlled, non-inferiority study comparing the perioperative (dis)continuation of aspirin in spinal surgery.

## Objectives

### Primary study outcome: composite of the following bleeding complications

Neurological deterioration as a result of hemorrhage in the surgical area with cauda and/or nerve root compression.Post-surgical anemia with hemoglobin level lower than 5 mmol/l, requiring transfusion.Subcutaneous hematoma leading to wound leakage and pain higher than NRS=7.Major and/or minor hemorrhage in any other body system according to the definition of the International Society on Thrombosis and Haemostasis bleeding scale.

### Secondary study outcomes

Each of the individual components of the primary outcomeAbsolute mean difference in operative blood loss between the study armsThrombo-embolic-related complications:Myocardial infarctionVenous thromboembolismStrokeArterial thromboembolism

### Primary outcomes: haemorrhage-related complications

#### Neurological deterioration as a result of hemorrhage in the surgical area with cauda and/or nerve root compression

The incidence of 30-day postoperative reoperation incidence is recorded in the hospital information system and recorded with a case record form at discharge from the hospital and during postoperative outpatient clinic visits. Of particular interest are directly hemorrhage-related reoperations. The aforementioned surgical site hemorrhages and postoperative subcutaneous, epidural or subdural hematomas are infrequent complications of spinal surgery. In case these hemorrhages excerpt pressure on the surrounding neurologic structures (e.g., cauda equine, nerve roots, or peripheral nerves) a rapid evacuation of the hematoma is required. Furthermore, perioperative hemorrhage-related complications can also result in an indirect need for reoperation. For instance, suboptimal nervous tissue decompression or tumor removal due to excessive bleeding during surgery might result in a need for reoperation. Therefore, the overall 30-day reoperation rate is recorded and compared among both treatment groups.

#### Post-surgical anemia with hemoglobin level lower than 5 mmol/l, needing transfusion

In case of peri- and/or post-operative blood loss leading to symptomatic anemia, objectified with laboratory research, with a hemoglobin level lower than 5 mmol/l a hemoglobin transfusion will be indicated.

Excessive perioperative blood loss can require postoperative allogeneic blood transfusions. The postoperative need for allogenic blood transfusions is registered in the hospital information system and is recorded with a case record form at discharge from the hospital.

The use of autologous blood transfusion is restricted to patients undergoing extensive surgical procedures with high expected blood loss. At the discretion of the surgeon or the anesthesiologist, a cell-saver autologous blood recovery system can be used during surgery. Blood recovered by this system is considered perioperative blood loss. In case a significant amount of blood is recovered and the patient is likely to benefit from an autologous transfusion, autologous blood will be transfused back to the patient.

#### Subcutaneous hematoma leading to wound leakage and pain score

Hemorrhage-related complications include surgical site hemorrhages and postoperative subcutaneous, epidural, or subdural hematomas. Hemorrhage-related complications resulting in an increased length of hospital stay or that require either invasive or non-invasive treatment are recorded in the hospital information system and are recorded with a case record form that is to be filled out at the time of discharge from the hospital and during postoperative outpatient clinic visits. Pain scores will be registered as well, as subcutaneous hematomas can lead to increased discomfort. Pain scores higher than 7 according to the Numeric Rating Scale (NRS) will be registered in the database. Potentially, some complications of spinal surgery can also be indirectly attributed to hemorrhage-related complications. For instance, surgical site hematomas are associated with an increased incidence of postoperative infections. Therefore, the overall 30-day complication rate is recorded and compared among both treatment groups.

#### Hemorrhage in any other body system

Hemorrhage in any other body system within 30 days post-surgery will be noted and compared between groups. These will be classified according to the International Society on Thrombosis and Haemostasis bleeding scale (ISTH-scale) [21].

### Secondary objective

#### All separate primary outcomes individually

##### Absolute mean difference in operative blood loss between the study arms

Perioperative blood loss is determined by measuring blood recovered in the suction device during surgery and weighting of blood-saturated gauzes used during surgery. The Validated Intraoperative Bleeding Scale (VIBe scale) will be used in order to objectify the intraoperative bleeding severity [22]. All cases will receive a vacuum drainage system applied to the surgical wounds in order to record the postoperative blood loss in the first 24 h. Blood loss is registered in the hospital information system and recorded with a case record form that is to be filled out at the time of discharge from the hospital.

##### Thrombo-embolic-related complications

*Myocardial infarction:* myocardial ischemic events diagnosed by a cardiologist according to the fourth universal definition of myocardial infarction.

*Stroke:* diagnosed by a neurologist defined as an acute or transient neurological deterioration with a positive radiological finding for a cerebral ischemic event.

*Venous thromboembolism:* diagnosed by a vascular internist defined as a concordant clinical presentation with a modified Wells score higher than 3, a positive D-dimer level > ng/mL, and a positive ultrasonographical examination.

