##### Arterial thromboembolism

All 30-day complications perioperative after spinal surgery are recorded. The incidence of all thrombo-embolic events is of interest in order to assess to compare the occurrence between the control and study group. During hospital stay and at regular postoperative outpatient clinical appointments within 6–12 weeks after surgery all perioperative complications are recorded and evaluated in a standardized manner using a case record form. Complications are classified according to a hospital database thesaurus and the severity of the complication is graded (see Table 1).

**Table 1 Tab1:** Grading of complications according to Clavien-Dindo

Grade	Description
1A	Recovery after non-invasive treatment (e.g., medication, physical therapy)
1B	Recovery after invasive treatment (except for operation in an OR) or admission to intensive care
2	Recovery after (re-)operation in an OR
3A	Complication still persists or is treated at the time of registration
3B	Complication resulting in permanent loss of function or disability
4	Death

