##### Thrombo-embolic-related complications

*Myocardial infarction:* myocardial ischemic events diagnosed by a cardiologist according to the fourth universal definition of myocardial infarction.

*Stroke:* diagnosed by a neurologist defined as an acute or transient neurological deterioration with a positive radiological finding for a cerebral ischemic event.

*Venous thromboembolism:* diagnosed by a vascular internist defined as a concordant clinical presentation with a modified Wells score higher than 3, a positive D-dimer level > ng/mL, and a positive ultrasonographical examination.

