### AEs, SAEs, and SUSARs

#### Adverse events (AEs)

Hemorrhage-related complications such as hemorrhage itself, hemorrhage-related neurological deficits such as paresis, anesthesia and cauda syndrome, anemia, hypotension, and increased infection risk.

Thrombo-embolic complications, i.e., myocardial infarction, increase of symptomatic coronary artery disease, brain stroke, or transient ischemic attack will be reported as well.

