### Adjucation commission

An adjucation commission will be assembled and assigned in order to assess the correct classification of complications. The commission will consist of a vascular internist, a cardiologist, and a neurosurgeon.

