## Statistical analysis

### Co-primary study parameter(s)

Statistical analysis will be performed using SPSS. The risk of hemorrhagic complications and reduction in thrombo-embolic perioperative events within 30 days after surgery will be compared by calculating the confidence intervals of both groups and noninferiority will be claimed if the complication risk percentage stays below 6.1 percentage points.

In order to compare the effect of predefined risk factors on the primary and secondary outcome (Table 2) a multivariate regression model with an intention to treat analysis will be used.

**Table 2 Tab2:** Predefined risk factors

Age	
Sex	
Type of operation Type of spinal procedure: non-instrumented decompression, fusion procedures, spinal level, degenerative, neoplastic	
Duration of surgery	
Amount of preoperative thrombocytes	
Prescribed aspirin dose (80 or 100 mg)	
Previous cardiac or cerebral infarctions (as well as coronary artery disease and transient ischemic attack)	
Duration of surgery	
Type of spinal surgery	

Additional outcomes will be the hemorrhagic outcome measures (perioperative blood loss, hemorrhage-related complications, need for reoperation, and transfusion requirement) that will be compared among both treatment groups with a chi-square or Student’s *t*-test. The treatment group bleeding risk is assumed to be below 0,0710 under the null hypothesis of inferiority.

Follow-up within the study ends at day 30 after surgery. All events after day 30 will not be registered for the Aspin trial. Incidental findings will be registered as well and assigned to the involved organ system.

In case of missing data, patients of the treating surgeon can be contacted to complete the missing information.

All efforts will be made to assemble data for the primary outcome analysis. In case this data is missing, participants will be excluded from the final analysis.

All patients randomized to one of the study arms will be analyzed according to the intention to treat analysis.

Missing data in baseline characteristics will be imputed using multiple imputation (*n*=10) based on the outcome and relevant baseline covariates using the “Multivariate Imputation by Chained Equations” (MICE) algorithm. Patients with missing primary outcomes will be excluded but every effort will be made to obtain follow-up.

The ACTS scale and PROMIS Global-10 score will be compared between pre- and postoperative assessment and between the study and control groups.

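### The venous thromboembolism definition requires a Wells score above 3, a positive D-dimer and a positive ultrasound together, so some proven venous events would not count towards this secondary outcome

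*Protocol article*

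**What the plan says.** The definition appears twice in the protocol article in the same words, under Thrombo-embolic-related complications in the Objectives and again in the Methods. A vascular internist makes the diagnosis, which is "a concordant clinical presentation with a modified Wells score higher than 3" together with "a positive D-dimer level > ng/mL, and a positive ultrasonographical examination". No alternative is offered.

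The surrounding text bears on how the definition works:

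- The Abstract and both Secondary study outcomes lists name venous thromboembolism as one of four thrombo-embolic components, beside myocardial infarction, stroke and arterial thromboembolism.
- The Arterial thromboembolism section says that "All 30-day complications perioperative after spinal surgery are recorded", and that the incidence of thrombo-embolic events of every kind is to be compared between the arms.
- The section headed Adjucation commission sets up a panel "in order to assess the correct classification of complications". It gives the panel no separate criteria.
- The Adverse events section says "Thrombo-embolic complications, i.e., myocardial infarction, increase of symptomatic coronary artery disease, brain stroke, or transient ischemic attack will be reported". No venous event is on that list.
- The Statistical analysis section, under a co-primary heading, says "The risk of hemorrhagic complications and reduction in thrombo-embolic perioperative events within 30 days after surgery will be compared".

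Pulmonary embolism is not mentioned anywhere in the article.

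**The concern.** A definition used to count an outcome should include the events that carry the outcome's name once they are proven. Here a pre-test clinical score and a laboratory result are conditions on top of imaging proof, and the only imaging accepted is ultrasound. A clot seen on ultrasound can therefore fail because the score was 3 or less, or because the D-dimer was not positive or not drawn. An embolism shown on chest imaging fails if no ultrasound was positive.

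What is at stake is the count for one component of a secondary outcome. If few venous events occur, losing even one or two makes the reported comparison less informative. The reported figure would also not be the incidence of all thrombo-embolic events that the protocol says it wants.

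**Working it through.** **Step 1. What the wording requires.** The phrase "modified Wells score higher than 3, a positive D-dimer level > ng/mL, and a positive ultrasonographical examination" is a list closed by 'and'. An event counts only if Wells > 3 AND D-dimer positive AND ultrasound positive. Applied to five kinds of event:

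| Event | Wells > 3 | D-dimer positive | Ultrasound positive | Counts as written | Counts if imaging-confirmed |
|---|---|---|---|---|---|
| Deep vein thrombosis meeting all three | yes | yes | yes | yes | yes |
| Deep vein thrombosis on ultrasound, score 3 or less | no | either | yes | **no** | yes |
| Deep vein thrombosis on ultrasound, D-dimer negative or not drawn | either | no | yes | **no** | yes |
| Pulmonary embolism on other imaging, no positive ultrasound | either | either | no | **no** | yes |
| Pulmonary embolism on other imaging, also meeting all three | yes | yes | yes | yes | yes |

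Three of the five are proven events that the rule rejects. The last row matters: pulmonary embolism is not excluded as a class.

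**Step 2. Comparison with the neighbouring definition.** Stroke, in the same section, needs a clinical picture and a positive radiological finding. Venous thromboembolism adds a score threshold and a laboratory result to the clinical picture and the imaging.

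**Step 3. Whether another section repairs it.** Recording all 30-day complications captures the event as a complication, classified by a hospital thesaurus and graded, but does not make it a venous thromboembolism. The adjudication section supplies no wider criterion. The adverse event list names no venous event.

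**Step 4. Effect on the sample size.** The plan's own figure uses bleeding only: 1% against 3%, a margin of 6.1 points, one-sided 0.025 and 80% power. The score-test formula is n = [(z₀.₉₇₅·s₀ + z₀.₈₀·s₁)/(0.061 − 0.02)]².

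- s₀ uses the proportions constrained to differ by 0.061 (0.0673 and 0.0063): s₀ = √(0.0673×0.9327 + 0.0063×0.9937) ≈ 0.2627.
- s₁ = √(0.03×0.97 + 0.01×0.99) = √0.039 ≈ 0.1975.
- n = [(1.960×0.2627 + 0.842×0.1975)/0.041]² ≈ 275.9, so 276 per arm against the stated 277.

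The figure is essentially reproduced. No venous event rate enters it, so changing the definition leaves it as it is.

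**Step 5. Possible size.** The documents give no venous event rate and no share of pulmonary embolism. Purely as an illustration, assume 1–2% of patients have a venous event and 20–50% of those are embolisms without a positive ultrasound:

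- Events per arm: 277×0.01 = 2.8 to 277×0.02 = 5.5.
- Not counted per arm: 2.8×0.20 ≈ 0.6 to 5.5×0.50 ≈ 2.8.

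Both ranges are assumptions. The illustration leaves out thromboses rejected on Wells score or D-dimer, for which the documents give no basis either.

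**The case against.** The strongest reply has several parts.

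- *The events are not lost.* This is correct. They are recorded as 30-day complications, and the overall 30-day complication rate is compared between the arms. What fails is the venous thromboembolism label.
- *Adjudication would deal with it.* The panel includes a vascular internist, and nothing in the article binds it to the literal wording. A reader might infer that it must reject these events, but the documents do not say so. They also give it no other criterion. It either follows the text and rejects proven events, or counts them under a rule that is not written down.
- *This is a condensed article.* The full protocol may say more about pulmonary embolism. The point, however, rests on an explicit definition stated twice and not on an omission. The missing number after the D-dimer inequality sign may be a gap in the text and plays no part here.
- *Strict criteria are defensible in an open-label trial, and they apply to both arms.* Objective confirmation is sensible, but imaging proof already provides it. A reader might infer bias between the arms, and the documents do not show any.
- *Venous events are peripheral.* This largely stands. The stated rationale concerns cardiac and neurologic thrombosis, and the Escape medication section gives both arms heparin prophylaxis against venous thromboembolism. That lowers the weight of the point without correcting the definition.

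**Conclusion.** The point holds in a limited form. As written, the definition misclassifies some proven venous events and does not fit the protocol's stated interest in all thrombo-embolic events. The change is worth making because it is specific and cheap, but its effect is probably small.

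Three stronger readings should be avoided:

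- That pulmonary embolism as such is dropped. One that also meets all three criteria still counts.
- That a co-primary outcome is damaged. The Statistical analysis heading uses that term, but the Abstract and both outcome lists place thrombo-embolic complications among the secondary outcomes, and the sample size rests on bleeding alone.
- That up to half of the events would be missed. That figure is only the upper end of an assumed range. The documents support no number.

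The conclusion rests on reading the three conditions as jointly required, which is the plain sense of the text, and on no wider definition standing in the full protocol. The bleeding composite, its margin and the sample size are unaffected.

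**What to change.** For endpoint classification only, define venous thromboembolism as either deep vein thrombosis confirmed by ultrasound or other imaging, or pulmonary embolism confirmed by imaging or autopsy. Record the Wells score and D-dimer where available as descriptors, not as conditions for counting. Use the same wording in both places where the definition appears and on the adjudication form, so that the panel works to a written criterion. If the full protocol already has a wider definition, bring the two texts into line.

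The cost is the revised wording and form. The change uses diagnoses made in routine care and adds no tests, visits or patients. It leaves the clinical work-up as it is.
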